**Figure 2 F2:**
[figure not shown]
Study design with two-arms randomization (hypnosis and CBT), 6 sessions each. Flexibility in terms of sessions is foreseen, i.e., a patient may have a session shifted by 1 or 2 weeks depending on its WHO performance status and/or the therapist's availability. This takes into account the toxicities, need to always have the same practitioner for the 6 sessions, and the reality of the field (absences, vacations, etc.).

At T1, after the interventions, patients will be asked to complete again the QLQ-C30, MFI, EVA fatigue and the ISQ-8 (see Table 2). They also will be interviewed by a trained psychologist about their acceptation of the program with semi-directed interviews. The interviews will be semi-structured to obtain as much information as possible. A first general question will ask about their general opinion of the program. Then, they will be asked to talk about their reasons for agreeing to participate in the program, as well as information about the implementation. Patients will answer whether the program seemed suitable or not and finally, whether they would recommend it to others. Each question will be as broad as possible, and then participants will be prompted if more detail is needed. Patients who would like to end their participation in the program prematurely will also be invited to participate in these interviews, as the reasons for non-adherence are among the evaluation criteria.

At the end, regardless of the inclusion arm, patients will receive one intervention over a period of 6 weeks and will be re-interviewed 3 months after the procedure (T2) on their level of fatigue and quality of life, representing 5 months involvement in total.

### Statistical considerations

The primary outcome will be analyzed in each intervention group. The proportions of patients who adhered to each intervention program (Hypnosis and CBT) will be presented with their two-sided 95% confidence intervals (95% CI), as the proportion of patients giving consent to participate in the study among the eligible patients at the screening who were offered the study. All statistical analyses of the secondary criteria will be done by group. Categorical variables will be described by the number of observations (N) and the frequency (%). Missing categories will be counted. Quantitative variables will be described by the number of observations (N), mean, standard deviation, median, minimum, and maximum. In case of missing data no imputation method will be used.

For the comparison of qualitative variables, a chi-square test or a Fisher's exact test will be used if the theoretical number of observations is <5. For the comparison of quantitative variables, a Student's *t-*test or a Kruskal-Wallis test will be used. For comparisons between two time points a Wilcoxon test for paired samples will be used. The correlation between the VAS values for fatigue and the scores on the MFI-10 questionnaire will be studied using Pearson's correlation coefficient or Spearman's correlation coefficient. The evolution of VAS fatigue values over the course of treatment will be modeled using linear mixed models to account for the repeated nature of the measurements. The analysis of the QLQC-38 questionnaire will be performed according to the EORTC guidelines.

All statistical tests will be two-sided and the significance level is set at 5% (i.e., *p* < 0.05). Statistical analyses will be performed with STATA v16 software and a statistical report will be provided according to the current model.

Program satisfaction will be assessed on the basis of the CSQ-8 score, SEQ evaluation of each session and put into perspective with the individual semi-structured interviews analyzed with QDA Miner. This is a mixed methods and qualitative data analysis software developed by Provalis Research. The program was designed to assist researchers in managing, coding and analyzing qualitative data. QDA Miner was first released in 2004 and the latest version 6 was released in September, 2020.

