### Population

#### Recruitment

Patients will be included in a French regional anticancer center. We plan to include 60 patients who will be allocated to each intervention group [i.e., Hypnosis (*n* = 30) and CBT (*n* = 30)]. The sample size will not be based on a power analysis but on the estimated recruitment capacity in the cancer institute.^1^ A recruitment of 30 patients per intervention group would allow us to estimate in each group a proportion of at least 80% of patients adhering to each intervention, with their 95% confidence intervals, of amplitude 0.28 (Machin et al., 2009).

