### Measures

In this feasibility study, the primary endpoint is the proportion of patients who have adhered to the proposed intervention program (both CBT and hypnosis programs include 6 sessions). A patient will be considered adherent if she/he participated in at least 4 of the 6 proposed intervention sessions. Adherence is defined in the same way in each intervention group. The choice to consider adherence to the programs at 4 out of 6 sessions is a commonly accepted practice in non-medication intervention studies (Brebach et al., 2016). Thus, patients participating in the study will have to receive at least 4 sessions (addressing key issues related to fatigue) in order to consider the program beneficial (hypnosis or CBT).

There are secondary quantitative and qualitative endpoints:

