c * E-health application; MFI-20, Multidimensional Fatigue Inventory; QLQ-C30, Quality of Life Questionnaire – Cancer; Score EPICES, precariousness and social inequalities in health; SEQ, session evaluation questionnaire; CSQ-8, satisfaction questionnaire about interventions*.

Randomization procedure. If the patient meets all the inclusion criteria and return the consent at T0, Biometrics Unit will proceed with the randomization and return the assigned treatment arm to the investigator. This form should also be completed and submitted for patients who meet the inclusion criteria but do not agree to participate in the study. A specific section of the form will be dedicated to them in order to register these patients (this will allow to answer the first secondary objective; i.e., the acceptance of participation in the study). The randomization procedure using the random block method will allocate the Hypnosis or CBT treatments with a 1:1 ratio and will be stratified according to two factors with two modalities: the number of lines of chemotherapy (2nd or 3rd line) and the management by the support care platform in the hospital (yes, no). Regarding stratification, the number of lines of treatment may have an impact on the primary endpoint (increase in fatigue) since it implies a non-response to treatment, a progression of the disease, and possibly a deterioration in the patient's condition. Secondly, the patients received at the Center may be offered support care as part of their standard care (*e.g.*, nutritional follow-up), and this may also have an impact on the primary endpoint (*e.g.*, reduction in fatigue). Therefore, these two factors will be considered as a stratification factor.

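### Any arm comparison of MFI and QLQ-C30 by the named tests would leave out the T0 score and both stratification factors, at a cost in precision

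*Protocol article*

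**What the plan says.** All places are in the protocol article.

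- **Statistical considerations, reporting.** "All statistical analyses of the secondary criteria will be done by group". Rules for descriptive statistics follow directly.
- **Statistical considerations, tests.** For comparing quantitative variables, a Student's t "test or a Kruskal-Wallis test will be used". Comparisons between two time points have their own test, a paired Wilcoxon. VAS fatigue over time gets a linear mixed model whose fixed effects are not listed. "All statistical tests will be two-sided and the significance level is set at 5" percent.
- **Procedure, randomisation.** Allocation is stratified by chemotherapy line (2nd or 3rd) and by management on the support-care platform (yes or no). The reason given for the first factor is that "the number of lines of treatment may have an impact on the primary endpoint (increase in fatigue"). The second factor is justified in the same way, by a possible reduction in fatigue.
- **Measures.** "the primary endpoint is the proportion of patients who have adhered to the proposed intervention program", with adherence meaning at least 4 of 6 sessions. Fatigue and quality of life are secondary.
- **Recruitment.** 30 patients per arm, and "The sample size will not be based on a power analysis but on the estimated recruitment capacity in the cancer institute".

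**The concern.** The strata were justified by their expected effect on fatigue, yet no analysis of fatigue names them. MFI and QLQ-C30 are measured at T0, yet the only test named for comparing such scores other than between time points cannot use the T0 value. With 30 patients per arm, a T0-adjusted analysis usually gives a clearly narrower interval for the arm difference at no cost in data.

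This matters because the article intends more than description. It sets two-sided 5% tests, and its Discussion expects the study to show which programme works best and for which fatigue profiles. A by-group report and within-arm paired tests cannot answer that, since a significant change in one arm and not in the other is not evidence of a difference between arms. A covariate-free two-sample test answers it less precisely than the collected data allow.

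Separately, calling fatigue the primary endpoint in the randomisation text contradicts the endpoint definition. It also leaves the choice of strata without a stated reason that relates to adherence.

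**Working it through.** **1. The plan's own figure.** The article states adherence of at least 80% in each group of 30 "with their 95% confidence intervals, of amplitude 0.28". For 24/30 the Wilson interval is 0.627 to 0.905, width 0.278. Jeffreys gives 0.279, and Wald gives 2 × 1.96 × √(0.8 × 0.2/30) = 0.286. The figure reproduces, and nothing below changes it or the total of 60.

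**2. What each named analysis uses.**

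| Analysis named | T0 score | Strata |
|---|---|---|
| Student's t or Kruskal-Wallis | no | no |
| Paired Wilcoxon between time points | yes, within patient | no |
| Linear mixed model, VAS | not stated | not stated |

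Time-point comparisons have their own test, so the natural reading of the first row is a comparison between the two arms. For MFI and QLQ-C30 no other arm comparison is named.

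**3. Precision forgone by omitting T0.** Inputs: 30 per arm and two-sided 5% (article); T0–T1 correlation r of 0.3 to 0.7 (assumption); equal SD in both arms (assumption). The residual variance after adjustment is (1 − r²) times the unadjusted variance.

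- Equivalent n per arm = 30/(1 − r²).
- Detectable difference at 80% power, in SD units = (1.960 + 0.842) × √(1 − r²) × √(2/30).
- Power at a difference of 0.5 SD = Φ(0.5/[√(1 − r²) × √(2/30)] − 1.960).

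| r | 1 − r² | Equivalent n per arm | Detectable difference (SD) | Power at 0.5 SD |
|---|---|---|---|---|
| unadjusted | 1.00 | 30 | 0.72 | 49% |
| 0.3 | 0.91 | 33 | 0.69 | 53% |
| 0.5 | 0.75 | 40 | 0.63 | 61% |
| 0.7 | 0.51 | 59 | 0.52 | 77% |

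The 0.5 SD is only a yardstick, since the article gives no target effect. Entry requires a fatigue VAS of at least 4, which narrows the T0 range and may keep r towards the lower end. The model costs few degrees of freedom: 60 − 5 = 55 residual against 60 − 2 = 58.

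**4. Ignoring the strata.** Suppose the strata are perfectly balanced by design and explain a share R² of the outcome variance (assumption, 0.05 to 0.30). The true error rate of a nominal 5% unadjusted test is then 2 × [1 − Φ(1.96/√(1 − R²))].

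| R² | True two-sided error |
|---|---|
| 0.05 | 4.4% |
| 0.10 | 3.9% |
| 0.20 | 2.8% |
| 0.30 | 1.9% |

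The test is conservative, so the loss is power and interval width.

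**The case against.** The case on the other side is substantial. The article condenses a fuller protocol, and covariates are often specified elsewhere. The sentence on t and Kruskal-Wallis tests is a general toolbox that is not tied to MFI or QLQ-C30, and it also covers the satisfaction scores, which have no T0 value. The primary endpoint is adherence, estimated per arm. The fatigue and quality-of-life objectives are worded as pre/post assessment and description, and efficacy is left to a later three-arm trial.

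Much of this stands and limits the point. It does not remove it: for a two-arm comparison of MFI or QLQ-C30 the article has named a class of test that cannot take covariates, which differs from leaving covariates open.

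Four stronger readings are tempting, and the article does not support them.

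- A reader might infer that every fatigue analysis ignores baseline. The paired Wilcoxon uses T0 within patients. The VAS has a mixed model, with daily values planned from T0, and its covariates are unstated rather than excluded.
- A reader might take the by-group sentence as an unadjusted arm test. It is followed by descriptive statistics and reads as a reporting rule.
- A reader might infer that chance imbalance at T0 passes in full into the arm difference, or that the comparison is biased. With similar SDs at both visits only about r times the imbalance carries over. Under randomisation the raw comparison is unbiased, and its standard error already allows for chance imbalance.
- A reader might infer that the variance used to size the later trial is inflated. The article does not say that this study's variance will be used for that, and a raw SD is simply the marginal SD.

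**Conclusion.** The point holds for MFI and QLQ-C30. As the tests are named, an arm comparison would discard the T0 score and the two factors that the article itself expects to affect fatigue. For VAS the article is only silent on covariates.

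The size depends on a correlation that the article does not give. Across r = 0.3 to 0.7 the forgone reduction in residual variance is 9% to 49%. The effect of ignoring the strata rests on an assumed R² and goes in the conservative direction. Neither effect is bias or an inflated type I error, and the adherence analysis is untouched.

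Importance is modest in a feasibility study with descriptive fatigue and quality-of-life objectives. It rises because the Discussion expects a conclusion on which programme is more effective. The contradiction over the primary endpoint is certain and needs no assumption, but it is a matter of wording.

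**What to change.** 1. **MFI and QLQ-C30.** In Statistical considerations, replace the t or Kruskal-Wallis arm comparisons with ANCOVA at each visit, or one mixed model, including arm, T0 score, chemotherapy line and support-care platform. Report adjusted arm differences with 95% confidence intervals, labelled exploratory.
2. **VAS.** State the fixed effects of the mixed model: arm, time, arm-by-time, T0 value and the two strata. If T0 is a covariate, it should not also be an outcome in the series.
3. **Satisfaction scores.** These have no T0 value, so simple tests may stay.
4. **Randomisation text in Procedure.** Name fatigue as a secondary endpoint where it is now called primary, or give the reason why each factor is expected to affect adherence.

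The cost is a few lines of text. T0 scores and both strata are already collected, and visits, patient burden and the sample size stay as they are.

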### Procedure

Three time points will be considered: T0 corresponds to the patient' inclusion in the study (patient agreement and completion of the study questionnaires), T1 corresponds to the end of the intervention after 6-weeks of intervention (semi-directive interviews on the acceptability of the program and completion of the questionnaires), and T2 corresponds to a follow-up visit 3 months after the intervention (questionnaires).

During the medical consultation with the oncologist, eligible patients will be identified. After oncologist approval, only inclusion/non-inclusion criteria (including fatigue VAS) will be retrieved by the investigator. If eligible, a patient will receive the information letter and consent, and will be asked to return it for cure of chemotherapy N°1 (T0).

The investigator will collect the sociodemographic (including the Score EPICES) and the medical variables. She/he will also present a web application (smartphone or tablet), available on AppStore or PlayStore (“*Mon Essai Patient*”) from the company Exolis. Patients who are not comfortable with these tools have the option of having a paper format. This application allows to collect every data from the questionnaires, encourages the daily or weekly assessment and limits missing data because patients will receive a notification when a questionnaire must be completed. Then a clinical research associate will give the different self-questionnaires to the patient, responding her/his questions if necessary. As shown Table 2, the patient will fill out, during ~30 min, the MFI-20, theQLQ-C30, and the VAS fatigue.

**Table 2 T2:** Measurements used in the study.

**Measures**	**Screening**	**T0**	**6 weeks interventions**	**T1**	**T2**
Inclusion/non-inclusion criteria	X				
Information letter and consent		X^a^			
Sociodemographics and medical variables		X		X^b^	
EPICES score		X^c^			
Fatigue and Quality of Life:					
6. VAS fatigue (physical/emotional)	X	X	X^c^ Daily assessment		X^c^
7. MFI-20		X^c^		X^c^	X^c^
8. QLQ-C30		X^c^		X^c^	X^c^
Feasibility					
9. SEQ			X^c^		
			Weekly assessment		
10. ISQ-8				X^c^	
11. Qualitative interviews				X^c^	

a *Information letter and consent are delivered at screening and retrieved if inclusion at T0*;

b * if progression, relapse or change of treatment*;

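### MFI and QLQ-C30 change is tested only in patients with both scores, and disease status is not scheduled at T2, so loss linked to deterioration would make change look too favourable and could not be traced

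*Protocol article*

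**What the plan says.** The Statistical considerations section of the protocol article fixes two rules that act together. On missing data: "In case of missing data no imputation method will be used". On change over time: "For comparisons between two time points a Wilcoxon test for paired samples will be used". The second rule names no instrument. MFI and QLQ-C30 are both collected at T0, T1 and T2, so it is the only stated method for testing their change.

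VAS fatigue is treated differently: "The evolution of VAS fatigue values over the course of treatment will be modeled using linear mixed models". Daily VAS runs from T0 to T1 (Repeated measures), so this model does not clearly extend to the T2 value. For quality of life the section adds "The analysis of the QLQC-38 questionnaire will be performed according to the EORTC guidelines". The instrument is called QLQ-C30 everywhere else.

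Table 2 (Procedure) has a row for "Sociodemographics and medical variables", marked at T0 and at T1. The T1 mark carries the footnote "if progression, relapse or change of treatment". The T2 cell is empty, and the Procedure text describes T2 as questionnaires only, 3 months after the intervention.

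Eligibility requires disease that progressed after first-line metastatic chemotherapy, the start of a second or third line, WHO performance status up to 2, and fatigue of at least 4 on the VAS. Total involvement is about 5 months.

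**The concern.** A signed-rank test needs both members of a pair. With no imputation, a patient who has a T0 score but no T2 score contributes nothing to the T0-T2 comparison. In this population, the reasons for a missing T2 questionnaire are likely to include deterioration and death. If the patients lost are those whose fatigue or quality of life worsened, the remaining pairs show a better change than the randomized group experienced.

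The article lists fatigue change as an objective and tests at the two-sided 5% level. The Discussion expects the study to show which management is most effective and for which patients. Neither arm is untreated, so within-group change will attract attention as an efficacy signal. Without disease and vital status at T2, the analyst cannot show who is missing and why, or describe the condition of those who answered.

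**Working it through.** **The plan's own figure.** The only sample-size figure is a 95% interval of width 0.28 for 80% adherence with 30 patients per group. The Wilson width is 2z√[p(1−p)/n + z²/(4n²)] / (1 + z²/n). With p = 0.80, n = 30 and z = 1.96 it is 0.278, which rounds to 0.28. The figure reproduces. It concerns adherence and is not affected by this point.

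**Inputs for the bias check.** From the article: 30 patients per group, paired Wilcoxon, two-sided 5%, no imputation. The article gives no dropout or death rate and no correlation between visits, so these are assumptions:
- score SD 1 at each visit, correlation r = 0.5 or 0.7, true mean change 0;
- 20% to 40% missing at follow-up, which leaves 24 to 18 complete pairs out of 30;
- logistic dropout with an odds ratio of 2 or 3 per SD of whatever drives it.

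**Formulas.** Let m be the amount, in SD, by which the driver's mean among completers falls below its mean in all patients. For an odds ratio of 2 at 20% missing, m is about 0.13; for an odds ratio of 3 at 40% missing, about 0.35. A higher score means more fatigue, so a negative bias is a false improvement.
- Driver = worsening (change has SD √[2(1−r)]): complete-pair bias = −m√[2(1−r)]. At r = 0.5 this is −0.13 to −0.35. At r = 0.7 the factor is √0.6 = 0.775, giving −0.10 to −0.27.
- Driver = unseen follow-up level: bias = −(1−r)m. At r = 0.5 this is −0.06 to −0.18; at r = 0.7, −0.04 to −0.11.
- Driver = baseline level: bias = +(1−r)m, the same sizes with the opposite sign.
- Random loss: m = 0, so the bias is 0.

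**Results.** Simulation agrees with these formulas. It also gives the share of tests that falsely declare improvement (nominal 2.5%) and the bias of a likelihood estimate that uses all baselines, as a mixed model would.

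| What drives dropout (20% to 40% missing) | Complete-pair bias, SD | False improvement | Likelihood estimate, bias, SD |
|---|---|---|---|
| Worsening | −0.10 to −0.35 | about 9% to 33% | about −0.09 to −0.28 |
| Unseen follow-up level | −0.04 to −0.18 | about 4% to 10% | about −0.07 to −0.28 |
| Baseline level only | +0.04 to +0.18 | below 2.5% | 0 |
| Random | 0 | about 2.5% | 0 |

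**Reading the table.** The mixed model removes the bias when loss depends on scores already seen. It removes a minor part when loss follows worsening: the ratio to the complete-pair bias is about (1+r)/2, that is 0.75 at r = 0.5 and 0.85 at r = 0.7. When loss follows the unseen follow-up level, it is further from the truth than the complete pairs, by a factor of about 1 + r. It is therefore not a cure for informative loss.

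**The case against.** The strongest reply has four parts.

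1. *The main fatigue measure is already protected.* This stands. Daily VAS, with 49 planned assessments, has a linear mixed model that uses every available value. A reader might infer that all fatigue change is tested in complete pairs. The document does not support that; the point is confined to MFI and QLQ-C30.

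2. *Dropout is not ignored.* This stands in part. Reasons for non-adherence are an endpoint, early leavers are invited to interview, the application sends reminders, the number of observations is reported and missing categories are counted. Rules for death and sensitivity analyses may sit in a fuller document, and their absence here is not the point. The point is that the two rules the article does state lead to complete pairs.

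3. *An empty table cell is weak evidence.* This is a fair caution. The VAS row of Table 2 is also empty at T1, although the Procedure text has VAS completed then. For disease status at T2, however, the text does not fill the gap; it too describes T2 as questionnaires. Status may be obtainable from hospital records, which makes the gap easy to close.

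4. *The direction and size are assumed.* This stands. A reader might infer that the results must lean toward improvement because only the fittest remain. That does not follow. Each patient is compared with his or her own baseline, so being fitter at entry does not create apparent improvement; loss driven by baseline fatigue produces the reverse. The article's one completion figure, 88% completing all sessions in a feasibility study of CBT in advanced colorectal cancer, is not a questionnaire rate and does not establish 20% to 40% missing.

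**Conclusion.** The point holds for MFI and QLQ-C30. As written, T0-T1 and T0-T2 change on these scales describes patients who returned both questionnaires, and for T2 nothing scheduled records why the others did not. If loss is linked to worsening, which is plausible in this population but not shown by the document, complete-pair change is too favourable by about 0.1 to 0.35 SD at an assumed 20% to 40% missing, and false improvement appears in roughly 9% to 33% of tests. Under random loss there is no bias; under baseline-driven loss the bias is 0.04 to 0.18 SD the other way. All of these sizes rest on the assumed missing rates, correlations and odds ratios.

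The consequence is limited. Fatigue and quality of life are secondary and meant to generate hypotheses, and the quality-of-life objective is descriptive. The primary endpoint, attendance at 4 or more of 6 sessions, is untouched. Nor would knowing disease status at T2 attribute fatigue at T2 to the programs, since there is no untreated arm. The change is still worth making, because it is cheap and status at T2 cannot be recovered from the questionnaires.

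**What to change.** 1. In Statistical considerations, analyse MFI and QLQ-C30 over T0, T1 and T2 with a linear mixed model by group, using all available scores. Keep the paired Wilcoxon as a sensitivity analysis.
2. In Table 2, add vital status (with date of death), progression and change of treatment at T2, taken from the center's records.
3. Report questionnaire completion and patient status by arm and visit.
4. Word T2 results as applying to patients who were alive and responding.
5. Do not present results in patients still on the same treatment line as an estimate of program effect. That group is selected by a post-baseline event and would again describe the patients who did best.

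The cost is a change of analysis wording and one chart extraction per patient, at most 60. The planned VAS analysis already uses this kind of model. The limit is that the model assumes missing at random: it removes bias from loss explained by observed scores, but at best part of the bias from informative loss. Items 2 to 4 are therefore needed alongside item 1.
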